#### Eliciting Adverse Event Information

The investigator is to report all directly observed adverse events and all adverse events spontaneously reported by the patient. In addition, each patient will be questioned about adverse events.

#### Exposure in Utero

If any study patient becomes or is found to be pregnant while receiving a study medication or within 30 days of discontinuing study medication/product, the investigator is to submit a specific Pregnancy Record Form that includes the anticipated date of birth. The patient is then to be followed by the investigator until completion of the pregnancy, and report the outcome to Active Biotech AB

# STATISTICAL METHODS PLANNED, AND DETERMINATION OF SAMPLE SIZE

## Statistical and Analytical Plan

The safety population includes all patients who have received any amount of ABR-215757.

The intention to treat population includes all patients who have received any amount of ABR-215757.

The Per Protocol population includes all patients without major protocol violations. Both populations will be described with regard to baseline data and exposure descriptively.

The adverse events, number of events and number of patients, will be summarized for the safety population by severity, by system organ class and by preferred term. Related AEs will be summarized in the same way.

Laboratory values including biomarkers, assumed to be log-normally distributed, will be summarized by visit, both absolute value and the ratio versus day 0 (n, mean, standard deviation, standard error, geometric mean with error and 95% confidence interval, median, min, max, quartiles and a p-value indicating if the value is significantly changed from baseline).

Disease activity variables, assumed to be normally distributed, will be summarized by visit, both absolute value and absolute change since day 0 (n, mean, standard deviation, standard error, 95% confidence interval, median, min, max, quartiles and a p-value indicating if the value is significantly changed from baseline). The time adjusted area under curve (AUC) will be calculated for the change from day 0 for the disease activity variables and will be summarized as above.

Vital signs and ECG will be summarized by visit as above shown for disease activity variables.

The correlation between selected variables (changes in disease activity variables and ratios versus day 0 for biomarkers) will be shown in figures. The Spearmann correlation coefficient will also be shown. Further analysis will be performed based upon the found correlations.

The screening value will be used in case the day 0 value is missing.

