**Main study**

*Visit 1, Screening visit, Day -14 ± 7 days*

The following procedures/evaluations will be performed at this visit:

- Written Informed Consent Form – must be obtained before any study-related procedures are performed
- Assignment of screening number
- Demography
- Medical history
- Urine Pregnancy test (if applicable)
- Urine dipstick (urinalysis)
- Assignment of patient screening number
- Physical examination
- Height and weight
- Vital signs (pulse rate, blood pressure)
- 12 lead Electrocardiogram (ECG)
- Clinical Assessment – mRSS , Digital Ulcers
- Sampling for clinical chemistry, hematology and coagulation
- Blood Sampling (biomarkers)
- Adverse Event questioning
- Review concomitant medications(s)
- Eligibility Checklist

*Visit 2, Baseline visit, Day 0*

The following procedures/evaluations will be performed at this visit.:

- Quality of life questionnaires (to be completed by the patient)
- Urine Pregnancy test (if applicable)
- Urine dipstick (urinalysis)
- Weight
- Vital signs (pulse rate, blood pressure)
- 12 lead Electrocardiogram (ECG)
- Clinical Assessment – mRSS , Digital Ulcers
- Adverse Event Questioning
- Review of Concomitant Medications(s)
- Eligibility check
- Assignment of enrollment number
- Sampling for clinical chemistry, hematology and coagulation
- Blood sampling (biomarkers).
- Skin Biopsy
- Sampling for ABR-215757 concentration in plasma (Predose)
- Dispensing of study medication - The first dose of ABR-215757 should be taken at the clinic, after all baseline assessments have been performed

*Visit 3, Day 14 ± 3 days*

The following procedures/evaluations will be performed at this visit:

- Weight
- Vital signs (pulse rate, blood pressure)
- Adverse Event Questioning
- Review of Concomitant Medication
- Sampling for clinical chemistry, hematology and coagulation
- Blood sampling (Biomarkers)
- Sampling for ABR-215757 concentration in plasma (predose)
- The daily dose of ABR-215757 should be taken at the clinic, after all assessments have been performed.

*Visit 4, Day 28 ± 7 days*

The following procedures/evaluations will be performed at this visit:

- Urine Pregnancy test (if applicable)
- Urine Dipstick (urinalysis)
- Weight
- Vital signs (pulse rate, blood pressure)
- Clinical Assessment – mRSS, Digital Ulcers
- Adverse Event Questioning
- Review of Concomitant Medication(s)
- Sampling for clinical chemistry, hematology and coagulation
- Blood sampling (Biomarkers)

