## Disease Activity Measurements

Disease activity measurements will include the following assessments

- Modified Rodnan Skin Score (mRSS)
- Digital ulcers

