***Urin­aly­sis:***

Leukocytes, protein (or albumin) and blood (erythrocytes). Samples will be taken at visits 1,2,4,5 and 6

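### Digital ulcers fall under a normal-theory rule that will not suit discrete, probably zero-heavy data from 10 to 20 patients; dipstick urinalysis is not excluded from the log-normal ratio rule

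*Protocol*

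**What the plan says.** Section 6.1 (Statistical and Analytical Plan) sets the analysis by class of variable.

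- **Disease activity:** "Disease activity variables, assumed to be normally distributed, will be summarized by visit, both absolute value and absolute change since day 0". The summary includes mean, SD, SE, 95% confidence interval, median, range, quartiles and "a p-value indicating if the value is significantly changed from baseline". A time-adjusted AUC of the change gets the same treatment. No test is named.
- **Laboratory:** "Laboratory values including biomarkers, assumed to be log-normally distributed, will be summarized by visit, both absolute value and the ratio versus day 0". Geometric means with a 95% confidence interval and a p-value follow.

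Two other sections determine what falls into these classes.

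- Section 5.2 says "Disease activity measurements will include the following assessments" and lists mRSS and "Digital ulcers". It does not say whether ulcers are counted, recorded as present or absent, or recorded as new.
- Section 5.5.2.1 (Safety Laboratory Evaluations) contains a urinalysis entry: "Leukocytes, protein (or albumin) and blood (erythrocytes). Samples will be taken at visits 1,2,4,5 and 6". The visit lists in section 2.2 and Appendix 1 show that this is a dipstick test. The result scale is not stated.

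Section 6.1 makes no exception for either variable. Section 3.2 plans about 15 patients, at most 20, with at least 10 completers.

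**The concern.** A normal-theory rule is a reasonable working choice for mRSS, where entry requires a score of at least 16 and every patient contributes a value well above zero. Digital ulcers differ. Nothing in sections 3.3 or 3.4 requires a patient to have one, so patients without ulcers can enter and contribute zero at day 0 and often zero change. With 10 to 20 patients, the mean change may rest on a handful of people. The interval and p-value would be printed next to those for mRSS as though they were equally reliable.

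The laboratory rule has a related gap. A log-normal variable is strictly positive. A negative dipstick reading coded as zero has no logarithm and cannot be the denominator of a ratio. Coding it as some positive number makes the ratio computable but dependent on an arbitrary choice.

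At stake is the honest reporting of one of the two listed disease activity measurements and of one safety laboratory panel.

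**Working it through.** The protocol gives no significance level, power, ulcer frequency or dipstick frequency, so there is no figure to reproduce. The frequencies below are assumptions, shown as ranges.

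**1. Digital ulcers, counts.** Inputs: n = 10, 15 and 20 (section 3.2). Assumed: 20%, 30% or 40% of patients affected; count in an affected patient = 1 + Poisson(1 or 2), that is a mean of 2 or 3. No true mean change: each ulcer heals with probability 0.4, and affected patients gain new ulcers at a rate that balances this. For each of 40,000 simulated trials per setting:

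- test: t = mean change / (SD of change / √n), two-sided 5%; a trial with no variation counts as no rejection
- interval for the mean day 0 count: mean ± t(0.975, n−1) × SD/√n; true value = share affected × mean count

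| n | All changes zero | t-test rejects (nominal 5%) | 95% CI covers the mean count | Lower limit below zero |
|---|---|---|---|---|
| 10 | 3-25% | 0.1-1.1% | 79-92% | 54-85% |
| 15 | 1-12% | 0.5-2.7% | 88-93% | 20-77% |
| 20 | 0.1-6% | 1.1-3.8% | 87-93% | 5-59% |

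**2. Sensitivity to the count model.** With more variable counts (gamma-Poisson, 15-50% affected, mean 1.5-3), rejection is 0.03-1.6% at n=10 and 0.4-3.8% at n=20. Coverage falls to 64-87% and 76-90%.

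If new ulcers may instead arise in any patient at the same overall rate (first model otherwise unchanged), rejection moves to 1.6-4.3% at n=10 and 4.5-5.6% at n=20. The shortfall in the test therefore depends on changes being confined to patients who already have ulcers. The coverage shortfall for the mean count does not, because it concerns day 0 values only.

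**3. Digital ulcers, present/absent.** The chance that no patient has an ulcer at a given visit is (1 − p)^n. With p = 0.2 this is 0.8^10 = 0.107 at n=10 and 0.8^20 = 0.012 at n=20. The normal-theory interval then has zero width. This scale is no closer to normal than counts are.

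**4. Exact tests.** With k non-zero changes, all in one direction, the two-sided sign test gives p = 2 × 0.5^k: 0.5 for k=2, 0.0625 for k=5 and 0.031 for k=6. In the first model at n=10, 41-88% of trials have at most two non-zero changes. An exact test is valid there but almost never significant.

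**5. Dipstick.** If a share q of patients is negative (coded zero) on day 0, the chance of at least one undefined ratio is 1 − (1 − q)^n. With q = 0.3 this is 1 − 0.7^10 = 0.972 at n=10 and 1 − 0.7^20 = 0.999 at n=20. With q = 0.7 to 0.9, the expected number of patients out of 10 with a usable denominator is 10 × (1 − q) = 3 to 1.

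**The case against.** The case on the other side is substantial, and several parts of it stand.

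- **Scales and test are inferred.** The protocol does not call ulcers counts or dipstick results grades, and it names no test. The t-test figures apply only to the test that the normality assumption suggests.
- **A reader might infer that the ulcer summaries are undefined.** They are not. Means, changes and AUCs of counts can always be computed. Only the t statistic fails, when every change is zero. Median, range and quartiles are already planned alongside.
- **A reader might infer a risk of false claims of benefit.** The calculations do not show one. The test is conservative, or close to nominal if new ulcers can arise in anyone.
- **A reader might infer that the urinalysis summary cannot be produced as planned.** Section 6.1 does not name urinalysis. It is covered only through its place under the laboratory heading. The urine pregnancy test sits under the same heading, and nobody would take its log. The visit lists also show the dipstick separately from chemistry, hematology and coagulation. The authors may well have meant quantitative values only.
- **The replacement test brings no power**, as step 4 shows.
- **The setting is exploratory.** This is a single-arm study with no formal sample size, and no decision is tied to the ulcer p-value. The list in section 5.2 may also not be exhaustive.

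The objection that such detail belongs in the analysis plan does not fully succeed. The protocol has not left the matter open: it assigns a distribution to a whole class of variables, and a later plan would have to follow that or depart from it.

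**Conclusion.** The point holds in a limited form. As written, section 6.1 together with section 5.2 puts digital ulcers under a normal model that they are unlikely to follow on any plausible scale with 10 to 20 patients. Under the assumed frequencies (20-40% affected, mean 2-3 ulcers, changes confined to affected patients), a nominal 5% paired t-test rejects about 0.1-1% at n=10 and 1-4% at n=20. The 95% interval for the mean count covers about 79-92% and 87-93%, often with an impossible negative lower limit at n=10. These sizes depend on inputs that the protocol does not supply. The mismatch between a normal model and sparse discrete data does not.

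The dipstick point is secondary. It is an omitted exclusion in the laboratory rule, resting on the section heading rather than on an explicit plan to analyse dipstick ratios.

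The impact is minor. Disease activity and laboratory safety are secondary endpoints (section 1.4), and the primary biomarker endpoint is unaffected.

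**What to change.** In section 6.1:

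- Among the disease activity variables, limit the normal-theory summary (mean, confidence interval, p-value, AUC) to mRSS.
- For digital ulcers, report by visit the number of patients with any ulcer, the number with a new ulcer, and the median and range of the count. Take any p-value from an exact sign or exact signed-rank test, and accept that it will rarely be informative.
- Limit the log-normal ratio rule to continuous laboratory values and biomarkers. Summarise dipstick results as shifts between categories from day 0.

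In section 5.2, state what is recorded for digital ulcers at each visit. The new-ulcer row needs the record to tell new ulcers from existing ones; if it holds only a total, report patients whose count rose.

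The cost is a few lines of text and two simple tables, with no added visits or procedures. Digital ulcers lose a mean-change interval, but that interval could not be relied on. The gain is valid reporting, not power.

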## Determination of Sample Size

No formal sample size calculation is performed. However, about 10 evaluable patients is considered relevant for determining changes in disease related biomarkers in this exploratory study.

# APPENDICES

## APPENDIX 1: SCHEDULE OF INVESTIGATIONAL EVENTS

|  | **Main study** | | | | | | **Continuation**j | | |
| --- | --- | --- | --- | --- | --- | --- | --- | --- | --- |
|  | Screening within  14±7 days | Treatment | | | | Follow-up | Continuation treament | | ContinuationTelephone follow-upo |
| **WEEK** | **-2** | **0 (BLb)** | **2** | **4** | **8/EWf** | **12** | **16** | **28, 40…n** | **n+4** |
| **DAY** | **- 14** | **0** | **14c,e** | **28d,e** | **56d/EWf** | **84d** | **112** | **196, 280..m** | **m+28** |
| **Visit No.** | 1 | 2 | 3 | 4 | 5 | 6 | 7 | 8, 9…Np | N+1 |
| Written Informed Consenta | x |  |  |  |  |  |  |  |  |
| Assignment of screening number | x |  |  |  |  |  |  |  |  |
| Eligibility Checklist | x | x |  |  |  |  |  |  |  |
| Demography and Medical history | x |  |  |  |  |  |  |  |  |
| Urine Pregnancy test (if applicable) | x | x |  | x | x | x | x | x |  |
| Assignment of enrollment number |  | x |  |  |  |  |  |  |  |
|  |  |  |  |  |  |  |  |  |  |
| Physical Examination | x |  |  |  |  | x |  |  |  |
| Height and weighti | x | x | x | x | x | x |  |  |  |
| Vital signs (pulse rate, blood pressure) | x | x | x | x | x | x |  |  |  |
| ECG | x | x |  |  | x | x |  |  |  |
|  |  |  |  |  |  |  |  |  |  |
| Clinical Assessment - mRSS, digital ulcers | x | x |  | x | x | x | xk | xk |  |
| Blood Sampling (Biomarkers) | x | x | x | x | x | x |  |  |  |
| QOL |  | x |  |  | x | x |  |  |  |
| Skin Biopsies |  | x |  |  | x |  |  |  |  |
|  |  |  |  |  |  |  |  |  |  |
| Clin Chem / Hematology / Coagulation | x | x | x | x | x | x | xl | xl |  |
| Urine dipstick | x | x |  | x | x | x |  |  |  |
| PK Sampling for ABR-215757 (predose) |  | x | x | x | xg | xg |  |  |  |
|  |  |  |  |  |  |  |  |  |  |
| Adverse Event Questioning | x | x | x | x | x | x | x | x | x |
| Review of Concomitant Medication | x | x | x | x | x | x | x | x | x |
|  |  |  |  |  |  |  |  |  |  |
| Dispensing Study Medicationh |  | x |  | x |  | xm | x | xn |  |
| Retrieval of Unused Study Medication |  |  |  | x | x |  | x | x |  |
| Accountability of Study Medication and Review of Treatment Compliance |  |  |  | x | x |  | x | x |  |

a) The informed consent must be obtained before the beginning of all study-related procedures

b) BL – Baseline visit. All visit procedures should take place before the first dose of study medication

c) Day 14 visit should be performed on day 14±3 days after first dose of study medication

d) A visit window ± 7 days is allowed for all visits of the main study after the day 14 visit

e) If a patient withdraws prematurely from treatment, an early withdrawal visit containing all procedures of the day 56 visit should be performed preferably on the day after the last dose of study medication or otherwise as soon as possible after the last dose of ABR-215757

f) EW – Early Withdrawal visit. If a patient withdraws prematurely from treatment, an early withdrawal visit containing all procedures of the day 56 visit should be performed preferably on the day after the last dose of study medication or otherwise as soon as possible after the last dose of ABR-215757

g) On the day 56 and day 84 visits, sampling for assessment of ABR-215757 plasma levels is performed one day and 29 days, respectively, after the last dose of ABR-215757.

h) The daily dose of ABR-215757 should be taken at the clinic after all assessments have been performed.

i) Height will be measured at visit 1 only.

j) Patents will be offered to continue treatment after the main study at the investigator’s discretion. Study medication for treatment continuation will be dispensed at visit 6. Patients in continuation phase will be followed up in terms of safety and disease activity (mRSS) after 28±7 days and thereafter every 84±14 days (12 weeks). Treatment may continue until the next scheduled visit (Visit N) after the last patient entering the main study has reached visit 5/EW. Active Biotech will collect data from the continuation phase separately from the main study.

k) In continuation phase: mRSS only.

l) In continuation phase: CRP, AST, ALT, ALP, GGT and bilirubin only

m) Patients in continuation phase only

n) No dispensing of study medication at the last clinic visit (visit N).

o) Telephone follow-up 28±7 days after the last clinic visit.

p) End of treatment visit = The next scheduled visit (Visit N) after the last patient entering the main study has reached visit 5/EW

1. Patients will come for clinic visits every 84 ± 14 days (12 weeks). Treatment may continue until the next scheduled visit (visit N, day m = end of treatment visit) after the last patient entering the main study has reached visit 5/EW. [↑](#footnote-ref-2)
2. End of treatment visit = Next scheduled visit after the last patient entering the main study has reached visit 5/EW. [↑](#footnote-ref-3)

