**Continuation (optional)**

*Visit 7, Day 112 ± 7 days*

The following procedures/evaluations will be performed at this visit:

- Clinical Assessment – mRSS
- Urine Pregnancy test (if applicable)
- Adverse Event Questioning
- Review of Concomitant Medication(s)
- Sampling for clinical chemistry (CRP, AST, ALT, ALP, GGT and bilirubin)
- Retrieval of Unused Study Medication and Accountability of study Medication
- Review of Treatment Compliance
- Dispensing of study medication

*Visit 8, 9..N, Day 196, 280..m (± 14 days)[[1]](#footnote-2)*

The following procedures/evaluations will be performed at this visit:

- Clinical Assessment – mRSS
- Urine Pregnancy test (if applicable)
- Adverse Event Questioning
- Review of Concomitant Medication(s)
- Sampling for clinical chemistry (CRP, AST, ALT, ALP, GGT and bilirubin)
- Retrieval of Unused Study Medication and Accountability of study Medication
- Review of Treatment Compliance
- Dispensing of study medication (no dispensing at visit N = end of treatment visit)

*Continuation telephone follow-up, 28 ± 7 days after the end of treatment visit*

The following procedures/evaluations will be performed at this visit:

- Adverse Event Questioning
- Review of Concomitant Medication(s)

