## Removal of patients from therapy or assessment

Patients should stop study treatment for any of the following reasons:

- Increased disease activity requiring changes in SSc treatment
- Use of non-permitted concurrent therapy
- Pregnancy
- Non-compliance with the study drug (more than a total of 14 missed doses during the study) or study procedures.
- Lost to follow-up
- Occurrence of AEs that in the Investigators opinion, are not compatible with the continuation of patient participation in the study.

Patients are free to withdraw from the study at any time without providing reason (s) for withdrawal without prejudice to further treatment. Any patient can also be withdrawn from treatment on recommendation from the Investigator or the sponsor. The reason for withdrawal should be clearly described and documented in the CRF. For patients in the main study, an early withdrawal visit containing all procedures of the day 56 visit should, whenever possible and regardless of the reason for withdrawal, be performed, preferably on the day after the last dose of study medication or otherwise as soon as possible after the last dose of ABR-215757. In addition, a follow-up visit should be scheduled 4 weeks after the last dose of study medication.

Patients in the continuation phase who discontinue treatment should be called for a withdrawal visit containing the procedures of visit N[[2]](#footnote-3) as soon as possible after the last dose of ABR-215757. (see Appendix 1, Schedule of investigational events). A telephone follow-up should also be made 4 weeks after the last dose of study medication.

If a patient does not return for a scheduled visit, every effort should be made to contact the patient. In any circumstance, every effort should be made to document patient outcome.

Patients who are prematurely withdrawn from the study will not be replaced.

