***Clinical Chemistry:***

Sodium, potassium, aspartate-amino-transferase (ASAT/GOT), alanine-amino-transferase (ALAT/GPT), alkaline phosphatase (ALP), gamma-glutamyl-transferase (GGT), pancreatic amylase, creatinine, total biliru­bin, calcium, albumin, C-reactive protein (CRP). Visits 1 – 6 will include all above clinical chemistry assessments. For patients that participate in the continuation phase, assessments will include ASAT/GOT, ALAT/GPT, ALP, GGT, bilirubin and CRP.

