#### Vital Signs

Vital signs, including: weight, height (baseline only), blood pressure, heart rate, and body temperature will be documented. Supine blood pressure (systolic and diastolic) and pulse rate (over 1 minute) are to be measured in the same arm after a five-minute rest. The same method and the same cuff size should be used to measure blood pressure in each individual patient throughout the study. Vital signs will be recorded at visits 1 - 6.

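### Cheap safety improvement: the continuation phase restarts ABR-215757 with no maximum in days but schedules no potassium, creatinine or blood pressure after Visit 6, nominally 29 days off drug

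*Protocol*

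**What the plan says.** The reduced continuation schedule reads the same wherever it appears in the Protocol.

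- Appendix 1, footnote l: "In continuation phase: CRP, AST, ALT, ALP, GGT and bilirubin only".
- Section 2.2, continuation visits: "Sampling for clinical chemistry (CRP, AST, ALT, ALP, GGT and bilirubin"). The rest of each clinic visit is mRSS, a pregnancy test where applicable, adverse event and medication review, drug accountability, compliance and dispensing.
- Section 5.5.2.1, Clinical Chemistry, puts the full panel, including potassium and creatinine, at Visits 1 to 6. It then says: "For patients that participate in the continuation phase, assessments will include ASAT/GOT", and goes on to list ALT, ALP, GGT, bilirubin and CRP.
- Section 5.5.2.3: "Vital signs will be recorded at visits 1 - 6". The vital-signs row of Appendix 1 is blank after Visit 6.
- Section 3.5: a patient who stops during continuation "should be called for a withdrawal visit containing the procedures of visit N", so the withdrawal visit has the same reduced content. The last contact is a telephone call without tests.

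On timing, footnote g says that plasma sampling at days 56 and 84 "is performed one day and 29 days, respectively, after the last dose of ABR-215757". Footnote j has continuation drug dispensed at Visit 6, with follow-up "after 28±7 days and thereafter every 84±14 days (12 weeks"). It gives the stopping rule: "Treatment may continue until the next scheduled visit (Visit N) after the last patient entering the main study has reached visit 5/EW". No maximum number of days or visits is stated.

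**The concern.** Monitoring falls away as exposure may grow longer. Visit 6 supplies a sound baseline before the drug is restarted, but no later scheduled value can be compared with it. A symptomless rise in creatinine, shift in potassium or rise in blood pressure during continuation would be found only if someone ordered an unscheduled test. Adverse event questioning does not replace measurement: Section 5.5.3.1 counts test and laboratory abnormalities needing intervention or further work-up as adverse events, but they have to be measured first.

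The reasons for choosing these three measures lie in the protocol's own text on the population. Section 3.4 excludes ongoing scleroderma renal crisis, excludes GFR only below 30% of normal, and names hypokalemia as a risk factor for torsade de pointes. Section 2.1 allows ACE inhibitors, and neither that section nor the stable-dose list in Section 4.4.2 sets a stable-dose condition for them. What is at stake is patient safety only.

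**Working it through.** This is schedule arithmetic on nominal days.

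**1. Reproduce the 29 days.** Visit 5 (day 56) is one day after the last dose, so the last dose is on day 55. Visit 6: 84 − 55 = 29 days, which agrees with footnote g. With the last dose held at day 55, the ±7-day window gives 77 − 55 = 22 to 91 − 55 = 36 days. The Visit 6 values are therefore off drug.

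**2. Count scheduled checks of potassium, creatinine and blood pressure.**
- Main study: Visits 3 and 4 on dosing, plus Visit 5 one day after the last dose. The longest gap between scheduled values from Visit 3 on is 28 days (day 28 to 56, and day 56 to 84).
- Continuation: none at Visits 7 to N, at the withdrawal visit or at the telephone call.

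**3. Nominal re-exposure = visit day − 84.**

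| Visit | Day | Re-exposure (days) | Divided by 56 |
| --- | --- | --- | --- |
| 7 | 112 | 28 | 0.5 |
| 8 | 196 | 112 | 2.0 |
| 9 | 280 | 196 | 3.5 |

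The same 28, 112 and 196 days are the time since the last scheduled value. The windows can be read in two ways:
- Footnote j, chained: 21–35, then (21 + 70) to (35 + 98) = 91–133, then (91 + 70) to (133 + 98) = 161–231 days.
- Section 2.2, anchored to study days with Visit 6 at 84 ± 7: 14–42, 91–133 and 175–217 days.

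**4. Who gets that far.** Let R be the days between a patient's entry and the last patient's entry. The last patient reaches Visit 5 on this patient's day R + 56, and treatment stops at the next scheduled visit after that.
- Treated from Visit 6 to Visit 7: 84 ≤ R + 56, so R ≥ 28.
- Treated on from Visit 7 to Visit 8: 112 ≤ R + 56, so R ≥ 56.
- Treated on from Visit 8 to Visit 9: 196 ≤ R + 56, so R ≥ 140.
- The last patient has R = 0. The next scheduled visit after Visit 5 is Visit 6, so that patient cannot continue. At most 20 − 1 = 19 patients can be affected.

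**5. Range for the first patient.** The protocol gives no recruitment period, so these values of R are assumptions.

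| Assumed R (days) | Visit N (day) | Re-exposure (days) | Clinic visits without the three measures |
| --- | --- | --- | --- |
| 28 | 112 | 28 | 1 |
| 90 | 196 | 112 | 2 |
| 180 | 280 | 196 | 3 |
| 365 | 448 | 364 | 5 |
| 730 | 868 | 784 | 10 |

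**The case against.** The strongest reply is that the reduced panel is a deliberate choice, stated consistently, and that whether it is adequate depends on a drug safety profile that this document does not set out. Section 2.3 says earlier human and preclinical experience supports doses up to 3.0 mg/day, and no renal, potassium or blood-pressure toxicity is stated. Continuation is at the investigator's discretion, after six visits at which all three measures were scheduled. Adverse event review, CRP and liver tests go on, incompatible adverse events lead to stopping, and unscheduled tests are not barred. Hematology, coagulation, urine dipstick and ECG also end at Visit 6, so singling out three measures is a clinical preference.

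Most of this stands. It rules out calling the schedule an error and it lowers the priority. It does not supply a reason to drop the checks: Section 2.3 gives no treatment duration, and unscheduled tests depend on symptoms or initiative. That other tests stop as well makes the gap wider, not smaller.

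A reader might infer three stronger points that the document does not support.
- **Drug accumulation at low GFR.** Section 4.4.2 says elimination is almost wholly by CYP 3A4 metabolism. The GFR limit shows renal vulnerability in the patients, not a drug risk.
- **Open-ended treatment.** Footnotes j and p give an event-based stop; only a maximum in days is missing.
- **Multiplying the gap or its cost by all 20 patients through Visit 9.** The last patient cannot continue, and Visit 9 needs entry about 140 days or more before the last patient.

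**Conclusion.** The point holds as a cheap safety improvement. It is not an error, and the sections do not conflict. No on-drug potassium, creatinine or blood pressure value is scheduled during continuation, where nominal re-exposure can reach 2.0 times the main treatment at Visit 8 and 3.5 times at Visit 9. Those multiples describe exposure and visit spacing, not a level of risk. How many patients reach them depends on the unstated recruitment period; continuation is also optional, so the number is probably well below the ceiling of 19. The choice of these three measures is a clinical judgement for the sponsor. The primary biomarker analysis is unaffected, and the suggestion is optional in weight.

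**What to change.** At Visits 7 to N, add creatinine and potassium to the chemistry sample already drawn, and record pulse and blood pressure. Through Section 3.5 this also covers the continuation withdrawal visit. Amend to match: footnote l and the vital-signs row of Appendix 1, the continuation visit lists in Section 2.2, the last sentence of Clinical Chemistry in Section 5.5.2.1, and the visit list in Section 5.5.2.3.

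The cost is two analytes and one pulse and blood-pressure reading per patient per continuation clinic visit. For a patient who reaches Visit 9 that is 3 × 2 = 6 results and 3 readings. No new visit or venipuncture is needed. The protocol gives no prices, so calling this cheap is a judgement. The downside is a little laboratory and visit time and a protocol and CRF amendment.
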